## Abstract

**Background:**

Treatment recommendations for prevention of type 2 diabetes complications often require radical and life-long health behaviour changes. Observational studies based on Self-determination theory (SDT) propose substantial factors for the maintenance of behaviour changes and concomitant well-being, but experimental research is needed to develop and evaluate SDT-based interventions. The aims of this paper were to describe

1) the design of a trial assessing the effectiveness of a training course for practice-nurses in autonomy support on patient-perceived motivation, HbA1, cholesterol, and well-being among a diabetes population,

2) the actual intervention to a level of detail that allows its replication, and

3) the connection between SDT recommendations for health care-provider behaviour and the content of the training course.

**Methods/Design:**

The study is a cluster-randomised pragmatic trial including 40 Danish general practices with nurse-led diabetes consultations, and the associated diabetes population. The diabetes population was identified by registers (n = 4034).

The intervention was a 16-hour course with interactive training for practice nurses. The course was delivered over 4 afternoons at Aarhus University and one 1/2 hour visit to the practice by one of the course-teachers over a period of 10 months (0, 2, 5, 10 mths.). The intervention is depicted by a PaT Plot showing the timeline and the characteristics of the intervention components.

Effectiveness of the intervention will be assessed on the diabetes populations with regard to well-being (PAID, SF-12), HbA1c- and cholesterol-levels, perceived autonomy support (HCCQ), type of motivation (TSRQ), and perceived competence for diabetes care (PCD) 15-21 months after the core course; the completion of the second course afternoon. Data will be retrieved from registers and by questionnaires.

**Discussion:**

Challenges and advantages of the pragmatic design are discussed. In a real-world setting, this study will determine the impact on motivation, HbA1c, cholesterol, and well-being for people with diabetes by offering a training course in autonomy support to practice-nurses from general practices with nurse-led consultations.

**Trial registration:**

ClinicalTrials.gov: NCT01187069

## Background

A great body of evidence exists on treatment recommendations for preventing type 2 diabetes complications [1-3]. These recommendations often require radical and life-long health behaviour changes for people with type 2 diabetes. Self-determination theory (SDT) [4], a psychological theory on motivation, describes the importance of the quality of the motivation for making behaviour changes. The quality of motivation depends on whether the regulation of actions are imposed by others or oneself (controlled motivation) or by the true feeling of free choice and personal significance of the outcomes attained by the actions (autonomous motivation). In observational studies, autonomous motivation has been found to be associated with improved quality of life, improved medication adherence, less depression, better diet, and improved cholesterol- and A1C-levels among people with type 2 diabetes [5-8]. Furthermore, observational studies based on SDT propose that support from health care providers can influence the quality of motivation for behaviour changes among people with type 2 diabetes. In Denmark, type 2 diabetes care primarily is delivered in general practice. In Danish general practices, nurses provide an increasing number of tasks including diabetes consultations [9]. Accordingly, it is important to further develop the content of nurse-led diabetes consultations, and more research is needed to tailor interventions aiming to improve autonomy support for people with type 2 diabetes in general practice.

The aims of this paper were to describe

1. the design of a trial assessing the effectiveness of a training course for practice-nurses in autonomy support on patient-perceived motivation, HbA1, cholesterol, and well-being among a diabetes population,

2. the actual intervention to a level of detail that allows its replication, and

3. the connection between SDT recommendations for health care-provider behaviour and the content of the training course.

## Methods/Design

### Study design

The study was conducted as a cluster-randomised controlled trial highly pragmatic in attitude including 40 Danish general practices and their diabetes populations.

### The context

#### Danish general practice

In Denmark, general practice is the primary access to the health care system, and 98% of the Danish population are registered with a selected general practice. Danish general practices are independent contractors within the public health service; the regional health authorities and they are remunerated on a combination of fee-for-service and capitation basis (75/25). The publicly funded (pre-paid by taxes) health care system ensures all citizens free general practice service [10].

#### Practice nurses

Practice nurses are employed by the general practitioners. The nurses provide a variety of tasks depending on their competences and the organisation of the clinic. Common tasks include weight control, vaccination of adults, blood pressure checks, lung function tests, alcohol abuse treatment and dietary counseling [9]. Practice nurses are qualified registered nurses. Their training in Denmark lasts 31/2 year and consists of both a theoretical and a clinical part. After qualifying, Danish nurses have several opportunities for post graduate education. However, no diploma education for practice nurses was available at the beginning of the training course "Practice nurses and Type 2 diabetes".

### Recruitment

#### Practices

In August 2009, a questionnaire about nurses and type 2 diabetes-consultations and an invitation to participate in the present study were sent to 258 general practices (registration numbers) from the former county of Aarhus in Denmark (Figure 1). A total of 50 practice registration numbers corresponding to 40 different addresses were included in this study based on the following inclusion criteria:

**Figure 1 F1:**
[figure not shown]
**Flow diagram of inclusion, randomisation and allocated intervention received among 258 general practices assessed for eligibility, the former county of Aarhus, DK, 2009**. * People identified by an algorithm based on health registers 2008-2009, and associated with the practices in January 2011.

1) that more than 50% of the people with type 2 diabetes, who had participated in a diabetes-consultation during the past year from the project invitation-date, had attended a consultation with a nurse at least once (confirmed by the practice). A diabetes-consultation was defined as a consultation including examinations, such as blood tests and blood pressure measurement as well as a conversation about living with type 2 diabetes or treatment modalities, according to the three-month consultations in the National guidelines regarding type 2 diabetes care [11],

2) enrolment to the project before registration deadline (three weeks following the date of invitation).

To avoid contamination of the intervention to control-practices, practice registration numbers with the same addresses were defined as one practice. Thus, 40 practices were randomised into two groups, and allocated in a way that the distributions of associated patients were approximately the same in the two groups. Randomisation was performed by a statistician who was blinded to the identity of the practices.

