#### The diabetes population

The diabetes population associated with the included practices in January 2011 was retrieved from the Danish Regional Chronic Database where people with diabetes are identified by an algorithm based on health registers [12]. The health registers consisted of The National Patient Registry, The National Health Insurance Service Registry, the prescription database, and the laboratory databases in the region. People at the ages of 40-74 years in October 2009 who fulfilled one or more of the following criteria: 1) at least one redeemed prescription on diabetes-medication (ACT-code: A10A (insulin) or/and A10B (oral blood-glucose-lowering agents) during October 2008 - October 2009, 2) at least three HbA1c measurements during October 2008 - October 2009, and/or 3) at least one HbA1c ≥6,4% between April 2008-October 2009, were included in the study population (n = 4034).

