### Statistical analyses

The primary analyses will be based on the intention-to-treat principle. As baseline value, the average value of the values measured within the last 12 months before course start will be used. The follow up-value will be the average value of the values measured during the 6 months following 15 months after the core intervention. Effectiveness of the intervention on HbA1c and cholesterol levels will be estimated by the differences between the diabetes populations in the intervention practices and the control practices with regard to 1) mean follow up-HbA1c and cholesterol, and 2) proportions with HbA1c≥8%, and proportions with Total cholesterol ≥5 mmol/l. The differences will be adjusted for baseline values. Differences in the proportions of the diabetes populations with measurements performed will also be assessed. Effectiveness of the intervention on score for PAID, SF-12(mental health), HCCQ, TSRQ and PCSD will be assessed by the difference between the diabetes populations in the intervention practices compared to the control practices 16 months after the core intervention.

Differences in the primary outcomes will be adjusted for age, gender, ethnicity, educational-level, and redeemed diabetes medication in the baseline-period. The analyses will be based on mixed models with including practice as a random factor in order to adjust for correlation within practices. Per-protocol analyses, including practices confirming changed behaviour and people with diabetes confirming participation in a nurse-led diabetes consultation, will be performed. Furthermore, subgroup analyses will be performed with regard to age, gender, and educational-level.

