### Sample size and power

It was estimated that with a minimum of 30 practices, a difference on 0.5% in mean HbA1c could be detected with a power on 90% under the assumption that 50% of the diabetes population participated in a nurse-consultation.

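### Allocation was balanced on associated patients, but the stated analysis model has no term for that factor; if practice size predicts outcome, standard errors will be somewhat too large

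*Protocol article*

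**What the plan says.** **Allocation.** In the protocol article, Recruitment, Practices (the text after the Figure 1 caption), registration numbers sharing an address are treated as one practice. It continues: "Thus, 40 practices were randomised into two groups", and these were "allocated in a way that the distributions of associated patients were approximately the same in the two groups". The method (strata, pairs, minimisation or other) is not described, nor is the reason for balancing on this factor.

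**Analysis.** Under Statistical analyses: "Differences in the primary outcomes will be adjusted for age, gender, ethnicity, educational-level, and redeemed diabetes medication in the baseline-period". For HbA1c and cholesterol, "The differences will be adjusted for baseline values". Clustering is handled as follows: "The analyses will be based on mixed models with including practice as a random factor in order to adjust for correlation within practices". No practice-level fixed effect is named, for size or anything else. No covariates are named for the secondary outcomes.

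**Patient numbers.** The section on the diabetes population gives 4034 people. The link to practices dates from January 2011: "The diabetes population associated with the included practices in January 2011 was retrieved from the Danish Regional Chronic Database". The course ran from October 2009 to September 2010, so this count is later than the intervention.

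**The concern.** When a cluster-level factor constrains allocation, the arms are made alike on it. Whatever that factor contributes to the outcome then largely cancels from the treatment contrast. A model that omits the factor does not know this. It estimates between-practice variance from all differences between practices, including those due to size, and carries that total into the standard error.

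The random practice intercept is no substitute. It treats size-related differences as noise, whereas a fixed covariate removes them from the residual between-practice variance.

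What is at stake is precision. There are 40 randomised units. The article's Discussion already expects dilution: some intervention practices missed all or part of the course, some patients may not have attended a consultation, and people with type 1 diabetes are included. A test that is more conservative than it need be adds to the risk of missing a real effect.

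**Working it through.** **The plan's own figure.** Sample size and power states that "with a minimum of 30 practices, a difference on 0.5% in mean HbA1c could be detected with a power on 90" per cent. SD, ICC, significance level and cluster size are not given there, so this can be neither confirmed nor refuted. With assumed two-sided 5% significance, SD 1.0 to 1.5, ICC 0.01 to 0.10 and 50 or 101 people per practice, the number of practices needed for a 0.5% difference runs from 4 to 46. The present point does not depend on it.

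**Inputs.**
- From the article: 40 practices and 4034 people, so m = 4034/40 = 100.85, about 101 per practice.
- Assumed: ICC 0.01 to 0.05, and R², the share of between-practice variance that size explains after the other covariates.

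**Step 1: formula.** The variance of a practice mean is proportional to ICC + (1 − ICC)/m. Fitting size replaces ICC by ICC(1 − R²). With size balanced between the arms:

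SE with size / SE without size = √{[ICC(1 − R²) + (1 − ICC)/m] / [ICC + (1 − ICC)/m]}

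Example, ICC 0.03 and R² 0.10: 0.97/101 = 0.0096; numerator 0.0270 + 0.0096 = 0.0366; denominator 0.0300 + 0.0096 = 0.0396; ratio √0.924 = 0.961.

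| ICC | R² 0 | 0.02 | 0.05 | 0.10 | 0.20 | 0.30 |
|---|---|---|---|---|---|---|
| 0.01 | 1.000 | 0.995 | 0.987 | 0.974 | 0.948 | 0.921 |
| 0.03 | 1.000 | 0.992 | 0.981 | 0.961 | 0.921 | 0.879 |
| 0.05 | 1.000 | 0.992 | 0.979 | 0.957 | 0.912 | 0.865 |

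At ICC 0.03 to 0.05, R² of 0.02 to 0.10 therefore means a standard error about 1 to 4% smaller. R² of 0.30 means 12 to 14%. With 50 measured people per practice instead of 101, ICC 0.03 and R² 0.10 give 0.969, about 3%.

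**Step 2: simulation of practice means.** Assumed: 40 practices split 20:20, allocation in size-matched pairs, SD of log size 0.5, no treatment effect, 10,000 runs per setting. Here the share is of the variance of practice means, which is a different scale from Step 1. A Step 1 R² of 0.10 corresponds to 0.10 × 0.03/0.0396 = 0.076 at ICC 0.03 and 0.10 × 0.05/0.0594 = 0.084 at ICC 0.05.

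| Share of practice-mean variance due to size | Interval width, without / with size | Type I error without size (nominal 0.05) |
|---|---|---|
| 0 | 1.00 | 0.049 |
| 0.02 | 1.01 | 0.048 |
| 0.05 | 1.03 | 0.044 |
| 0.10 | 1.06 | 0.036 |
| 0.20 | 1.12 | 0.027 |
| 0.30 | 1.20 | 0.020 |

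With size in the model, type I error stays between 0.046 and 0.050. The widths agree with the exact-balance approximation 1/√(1 − share): 1.05 at 0.10 and 1.20 at 0.30.

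**Step 3: does balancing help even when size is not modelled?** At a share of 0.30, the actual standard deviation of the unadjusted estimate is 0.078 under paired allocation and 0.094 under simple randomisation. The unadjusted model reports an average standard error of about 0.093 in both cases. The gain is real, but the model does not report it.

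**The case against.** **Nothing shows that size matters.** The article gives no association between practice size and any outcome. What counts is the association left after the other covariates, and baseline adjustment may remove much of any stable link for HbA1c and cholesterol. This stands. It is why the effect can be given only as a range that starts at nil.

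**The arithmetic is favourable to the point.** Step 1 gives every practice 101 measured people, although questionnaires go unreturned and not everyone has a laboratory value. Fewer measured people reduce the gain. Step 2 assumes tight pairing, and looser balancing would reduce the effect. Both stand. Patient numbers are also the likely, but not the only, reading of the allocation sentence.

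**An analysis plan may add the term.** The article is condensed and does not call its covariate list exhaustive. That is fair, and silence alone would not be a finding. But the article does name an adjustment set, and that set does not match the design it describes.

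**Readings that go too far.** A reader might infer that the balancing was wasted. Step 3 shows otherwise: it still guards against chance imbalance and lowers the true variance of the estimate. A reader might also infer that the intervals are certainly too wide, or that the result could be biased or falsely positive. The first holds only if size is prognostic. The second is contradicted by the simulation, where every departure of the unadjusted test from 0.05 was on the conservative side.

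**Conclusion.** The point holds as a minor matter of efficiency and consistency. Allocation was constrained on associated patients, the stated model leaves that factor out, and the random practice effect does not replace it. If size predicts outcome after the other covariates, standard errors are overstated and tests conservative. The cost is nil with no such link and about 1 to 4% of the standard error for R² of 0.02 to 0.10 at ICC 0.03 to 0.05. It passes 10% only if size is strongly prognostic. These figures rest on the assumed ICC and R², about 101 people per practice, close balance, and reading the allocation factor as patient numbers. The article documents neither the ICC nor the size-outcome link, so no single figure should be attached to this trial. The validity of the treatment comparison is not in question.

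**What to change.** State how the allocation was balanced. Then add the patient count used at allocation, on the log scale, or the strata or pairs actually used, as a fixed practice-level covariate in all primary and secondary mixed models. Define it for the 40 randomised addresses rather than the 50 registration numbers. Do not use the January 2011 count, which is later than the course. Randomisation-based inference that respects the allocation constraint is an alternative.

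A single size covariate costs about one of 38 practice-level degrees of freedom. If size proves unrelated to outcome this is negligible: the simulated interval-width ratio was 0.999 (without / with size). Fitting strata or pairs costs more degrees of freedom. The count must have existed for the allocation to be balanced on it, but the article does not show that it was kept, so it may have to be recovered from the randomisation records.

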#### The diabetes population

The diabetes population associated with the included practices in January 2011 was retrieved from the Danish Regional Chronic Database where people with diabetes are identified by an algorithm based on health registers [12]. The health registers consisted of The National Patient Registry, The National Health Insurance Service Registry, the prescription database, and the laboratory databases in the region. People at the ages of 40-74 years in October 2009 who fulfilled one or more of the following criteria: 1) at least one redeemed prescription on diabetes-medication (ACT-code: A10A (insulin) or/and A10B (oral blood-glucose-lowering agents) during October 2008 - October 2009, 2) at least three HbA1c measurements during October 2008 - October 2009, and/or 3) at least one HbA1c ≥6,4% between April 2008-October 2009, were included in the study population (n = 4034).

### The intervention

The intervention was a training course for practice nurses delivered between October 2009 - September 2010.

The intervention was depicted by a PaT Plot, proposed by Perera et al, showing the timeline and the characteristics (fixed or flexible) of the intervention components [13] (Figure 2 and 3).

**Figure 2 F2:**
[figure not shown]
**Graphical depiction of the timeline and the content of the "Practice nurses and Type 2 diabetes"-intervention**. Squares reflect the fixed elements, e.g. printed materials. Circles reflect the activities that are flexible, e.g. interaction between participants. This graphical method was proposed by Perera et al [13],(part 1 - to be continued in Figure 3).

**Figure 3 F3:**
[figure not shown]
**Graphical depiction of the timeline and the content of the "Practice nurses and Type 2 diabetes"-intervention**. Squares reflect the fixed elements, e.g. printed materials. Circles reflect the activities that are flexible, e.g. interaction between participants. This graphical method was proposed by Perera et al [13], (part 2 - Figure 2 continued).

#### Underlying theory

The intervention was based on Self-determination theory (SDT), which describes different kinds of motivation and facilitators of improved and maintained motivation [4] (Figure 4). SDT distinguishes between autonomous and controlled motivation. The motivation is controlled, when actions are externally regulated or regulated by introjections, and the motivation is autonomous, when actions are regulated by identification or integrated. The process of being autonomously motivated to perform an activity in order to attain some separable outcome is called internalisation. According to Ryan and Deci, internalisation and integration can be facilitated by social conditions supporting basic psychological needs for autonomy, relatedness, and competence [4]. In other words, the feeling of choice and volition with respect to one's own goal or behaviour, the feeling of interest and support of others, and the feeling that one can accomplish the behaviours and reach the goal, are crucial for motivation, the persistence of the motivation, and well-being; And, satisfying these needs can be supported by important others, e.g. health care providers.

**Figure 4 F4:**
[figure not shown]
**The Self-Determination Continuum showing types of motivation with their regulatory styles and processes, adapted from **[4].

#### The connection between SDT-based recommendations on health care provider behaviour and the course content

Concrete recommendations on health care provider behaviour based on SDT have been suggested [14,15], and the training course for practice nurses described below was conducted to meet these recommendations.

#### Structure and process

The course was arranged as four-hour sessions over four afternoons. The course was initiated with two coherent afternoons comprising the core intervention, followed by two single afternoons with an implementation purpose, two and five months later. The practice nurses were paid their normal wages for participating in the course. Ten months after course-initiation, the practice nurses were given the opportunity to be visited in the practice by one of the course-teachers.

The teaching on the course was primarily performed by two nurses with several years experience of consultations for people with diabetes, autonomy support, and learning processes. The lesson about current treatment recommendations of people with type 2 diabetes was provided by a general practitioner, who was also an Associate Professor in general practice, and researcher in the field of type 2 diabetes.

The ratio between the presentations and interactive learning [16] was 1:3. The interactive learning was conducted in group exercises, work-shops, and plenum discussions, all supervised by the teachers. The teaching was intended to be autonomy-supportive, based on the evidence from the association between autonomy-supportive teaching climates and behavioural changes in the participants [17].

